### **Data Handling and Record Keeping**

To protect patient privacy, all research data would be handled in line with HA/Hospital's policy in handling/storage/destruction of patients' medical records. They would be locked in cabinets where the department or ward keeps patients' confidential information. Electronic data should be saved in secured computer of the hospital with restricted access. Files containing the audio records will be password-protected and encrypted and closed when computers will be left unattended. All electronic data will be stored in password-protected computers or files.

### **Data analysis**

The Statistical Package for Social Sciences (SPSS) software, version 25.0 for Windows (IBM Corp., Armonk NY, USA) will be used to analyze the data; all significance tests will be performed at a significance level of .05 (two-sided). Descriptive statistics will be used to calculate the mean scores, standard deviations, and score ranges of the various scales. The comparability of the two groups will be assessed using inferential statistics, including independent-samples *t*-tests and chi-squared tests. The normality of the data will be assessed using a normal probability plot and skewness statistic. Generalized estimating equation models will be used to examine the effect of the intervention on each outcome between groups over time; between-group effects, within-group (time) effects, and interaction effects (group-by-time) will be examined.

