### **Research Plan and Methodology**

#### ***Study design***

An assessor-blinded prospective RCT will be conducted in two pediatric outpatient clinics in two public hospitals in different districts of Hong Kong. The aim of the RCT is to examine the effects of a brief MI delivered to parents via mobile instant messaging on PA levels, cancer-related fatigue, handgrip strength (HGS), peak expiratory flow rates (PEFR), and QoL among Chinese pediatric cancer survivors. Participants will be recruited from the two pediatric

oncology outpatient clinics in Hong Kong. The parent-child dyads who meet the criteria will undergo baseline assessments before randomization. The method of simple complete randomization will be adopted. Subjects will be randomly allocated to experimental or control groups. Randomization will be performed by a research assistant opening a sequentially numbered, opaque sealed envelope with a card inside indicating the allocated group. The random numbers to be used for group assignment will be computer-generated by another research assistant before subjects recruitment begins. Allocation concealment will thus be ensured.

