### ***Sample size calculation***

We used power analysis to estimate the sample size, referring to the results of our previous pilot study of the intervention and findings of our previous intervention studies on efforts to promote PA among pediatric cancer survivors in Hong Kong. An average moderate effect size (Cohen's  $d = 0.5$ ) was found for the outcomes of PA and fatigue levels, muscle strength, and QoL. Consultation with an expert panel, comprising a pediatric oncologist, a nursing specialist in pediatric oncology, and a professor and assistant professor from a local university, indicated that this result can be regarded as the minimally important difference that warrants a change in patient management. To detect a statistically meaningful between-group difference with a moderate effect size (Cohen's  $d = 0.5$ ) and a power of 80% (two-tailed; with a potential attrition rate of 20%) at  $\alpha = .05$ , a minimum of 160 parent–child dyads with 80 dyads per arm will be required.

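### The GEE plan names no adjustment for the outcome score measured before randomisation and does not say how baseline enters the model; prespecified adjustment costs no large-sample precision and may add power

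*Combined protocol and SAP*

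**What the plan says.** Under Study design, parent–child dyads "will undergo baseline assessments before randomization", and for allocation "The method of simple complete randomization will be adopted".

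Under Outcome measures, the primary outcome is physical activity at 12 months. Baseline appears beside 1, 3, 6 and 12 months in the list of time points for the secondary outcomes, and both groups are assessed at all five visits.

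Under Data analysis, "The comparability of the two groups will be assessed using inferential statistics", with t-tests and chi-squared tests as the named methods. Then "Generalized estimating equation models will be used to examine the effect of the intervention on each outcome between groups over time", with group, time and group-by-time effects to be examined. No covariate is named there or elsewhere. The section does not say whether the baseline score is an outcome row, a covariate, or constrained equal between arms, and it does not say which term or contrast is the primary 12-month test.

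**The concern.** A pre-randomisation measurement of the outcome is usually the most useful covariate a trial has, and here it is already collected. If baseline is instead one of the time points in the GEE, the 12-month group-by-time contrast estimates a difference in change from baseline. That estimator is less efficient than baseline adjustment and, when the correlation is low, less efficient than ignoring baseline altogether.

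The comparability tests do not fill the gap. Allocation is random and concealed, so any baseline difference between arms is due to chance, and a p-value for it answers a question whose answer is known.

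At stake is the precision of the primary and secondary comparisons. So is clarity about which analysis the sample size supports, since several tests of different power fit the present wording.

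**Working it through.** **Inputs from the documents.** Two-sided alpha 0.05 (Data analysis). Under Sample size calculation: Cohen's d = 0.5, 80% power, 20% attrition, and "dyads with 80 dyads per arm will be required".

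**Assumed, because the documents do not give them.** The correlation ρ between baseline and 12-month scores, and the ratio q of the baseline SD to the 12-month SD. The 12-month SD is set to 1.

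**Step 1: reproduce the plan's figure.** A two-sample t-test (noncentral t) with d = 0.5 has 79.5% power at 63 per arm and 80.1% at 64. Allowing for attrition, 64 / 0.8 = 80 per arm, or 160 in total. This matches the plan exactly, so the sample size is that of an unadjusted comparison at one time point.

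**Step 2: variance of each 12-month estimator, relative to the unadjusted comparison.**
- Unadjusted: 1
- Change from baseline: 1 + q² − 2ρq, which is 2(1 − ρ) when q = 1
- Baseline-adjusted: 1 − ρ²

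Unadjusted minus adjusted is ρ². Change minus adjusted is (q − ρ)². Neither can be negative, so in large samples adjustment is never the less precise choice. Change beats ignoring baseline only if ρ > q/2.

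**Step 3: power at 64 per arm.** The effective standardised difference is 0.5 / √(variance), again with the noncentral t.

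| q | ρ | Variance, change | Variance, adjusted | Power, change | Power, adjusted |
|---|---|---|---|---|---|
| 1 | 0.3 | 1.40 | 0.91 | 66.0% | 83.7% |
| 1 | 0.4 | 1.20 | 0.84 | 72.7% | 86.5% |
| 1 | 0.5 | 1.00 | 0.75 | 80.1% | 90.0% |
| 1 | 0.7 | 0.60 | 0.51 | 95.2% | 97.6% |
| 0.5 | 0.3 | 0.95 | 0.91 | 82.1% | 83.7% |

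Unadjusted power is 80.1% in every row.

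**Step 4: the primary outcome.** Under Subjects, entry requires no physical exercise in the previous 6 months. The primary instrument, CUHK-PARCY, rates activity over the past six months from 0 to 10. Baseline scores should therefore lie near the floor with little spread, which points to q below 1. In the last row (q = 0.5, ρ = 0.3) the gain over change is 83.7 − 82.1 = 1.6 points, and over unadjusted it is 83.7 − 80.1 = 3.6 points. Grip strength, peak flow, fatigue and quality of life are not restricted at entry in this way, so the equal-SD rows are more plausible for them.

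**The case against.** The strongest reply is that the plan is underspecified rather than wrong. Three inferences that a reader might draw go further than the documents allow.

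- *Baseline is an outcome row.* This is the natural reading of Outcome measures together with Data analysis, but it is not stated. The list that includes baseline concerns the secondary outcomes, while the primary outcome is defined at 12 months. Data analysis lists effects to be examined, not a full model.
- *The trial misses its 80% power.* The sample size is correct for an unadjusted 12-month comparison. Among single 12-month contrasts, a shortfall requires a change contrast with ρ below q/2: below 0.5 at equal SDs, below 0.25 at half the SD. The entry rule makes equal SDs doubtful for the primary outcome.
- *The comparability tests will drive the choice of covariates.* The plan describes no such selection, and the tests do not themselves bias the treatment estimate. They are merely uninformative.

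It can also be said that stable age and sex differences in grip strength and peak flow would make ρ high, and change scores would then already remove most of that variation. At equal SDs and ρ = 0.7 the adjusted analysis gains only 97.6 − 95.2 = 2.4 points over change. That is fair, although the gain over an unadjusted comparison would then be large.

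What stands after these objections is that no baseline adjustment is named, the handling of baseline and the primary contrast are left open, and the comparability tests serve no purpose.

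**Conclusion.** The concern holds in this limited form. The plan names no adjustment for a score it already collects before randomisation, and it leaves open how that score enters the GEE. Adjustment cannot reduce large-sample precision, whatever the correlation or SDs.

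The size of the gain is unknown. With equal SDs, and for ρ from 0.3 to 0.7, it runs from about 18 down to 2 percentage points of power over a change contrast, and from about 4 up to 17 points over an unadjusted comparison. For the primary outcome it may be only a few points. These figures assume 64 evaluable children per arm, d = 0.5 and the stated values of ρ and q.

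The unadjusted analysis is valid but not the most efficient, and the documents do not show that the trial is underpowered. The change should be made because it is nearly free and removes an ambiguity in the primary test.

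**What to change.** In Data analysis:

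1. Name the between-group contrast at 12 months as the primary test. Fitting the post-baseline visits with a baseline covariate is not enough, because the group effect could then be an average over 1, 3, 6 and 12 months.
2. Estimate that contrast with the outcome's baseline value as a covariate, or with baseline means constrained equal between arms. The second option keeps children without a follow-up visit in the model, which fits the intention-to-treat commitment under Data collection. Apply the same approach to the secondary outcomes.
3. Prespecify age and hospital as covariates, and sex if it is recorded. Age and hospital are known from eligibility and recruitment, but no section shows that sex is collected, so the sponsor should confirm this.
4. Replace the t-tests and chi-squared tests of comparability with a descriptive table of baseline characteristics by arm.

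The cost is analysis wording and a few degrees of freedom. No extra participants, visits or outcome measurements are needed.

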### ***Subjects***

#### **a) Pediatric cancer survivors**

Hong Kong pediatric cancer survivors meeting the inclusion criteria will be invited to participate in this study. The inclusion criteria included (1) children aged from 9 to 16 years, (2) able to communicate in Cantonese and read Chinese, (3) have completed treatment for at least six months previously, (4) does not participate in physical exercise in the previous 6 months. Survivors with evidence of recurrence or secondary malignancies and those with physical impairment, cognitive impairment, or impaired mental status identified from their medical records will be excluded.

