### ***Outcome measures***

The primary outcome measure is the level of physical activity of the survivors at 12 months after starting the intervention. The secondary outcome measures are survivors' levels of fatigue, left- and right-HGS, PEFR and QoL at baseline, 1, 3, 6, and 12 months after starting the intervention. Participants in both groups will be required to complete the questionnaires and assessments at baseline (during their medical follow-up), 1, 3, 6 and 12 months after starting the intervention (during home visits).

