### (2) Left- and right-handgrip strength

Hand-held dynamometer (HHD) will be used to assess the survivors' right- and left-HGS. Before the measurement, the handle of the HHD will be adjusted to allow the base to rest on the first metacarpal (heel of palm) and the handle to rest on the middle of four fingers. During the test, subjects will be instructed to push as hard as they could, with their arms keeping at right angles and their elbows by the side of their bodies. The subjects will be asked to repeat the test three times with 10 to 20 seconds resting time in between each push. Only the highest of the three measurements in each subjects will be recorded.

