### (4) Peak expiratory flow rates

A mini-Wright Standard Handheld peak flow meter will be used to determine survivors' PEFR. It is a useful physiological test to assess an individual's lung functionality by measuring an individual's maximum speed of expiration. It was shown to be an accurate and precise device to determine an individual's pulmonary functionality.

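### Within-group time effects on handgrip strength and peak flow in growing children cannot show benefit; the plan should rest claims on a randomised contrast adjusted for baseline value, age and sex

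*Combined protocol and SAP*

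**What the plan says.** The Subjects section admits "children aged from 9 to 16 years". Outcome measures lists left and right handgrip strength (HGS) and peak expiratory flow rate (PEFR) among the secondary outcomes, measured at baseline and at 1, 3, 6 and 12 months. Baseline is taken at a clinic follow-up and all later assessments at home visits.

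The only HGS scoring rule is "Only the highest of the three measurements in each subjects will be recorded". For PEFR the plan says that a hand-held meter "will be used to determine survivors' PEFR". Neither section gives a conversion for age, sex or body size.

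Data analysis plans generalised estimating equations (GEE) for each outcome at a two-sided 5% level and says that "between-group effects, within-group (time) effects, and interaction effects (group-by-time) will be examined". It names no covariate and does not say which of the three effects is the estimate of benefit. Study design specifies simple randomisation, without stratification, and a concurrent control group.

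Sample size calculation treats d = 0.5 as the minimally important difference. It is an average that "was found for the outcomes of PA and fatigue levels, muscle strength, and QoL"; PEFR is not in that list.

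**The concern.** Grip strength and peak flow rise as children grow. Over 12 months both arms should improve on these outcomes even if the intervention does nothing. A time effect therefore mixes growth with any effect of the intervention. It also mixes in the change of setting, because only baseline is measured in the clinic.

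The Implications section anticipates better physiological outcomes. With three effects examined and none designated, a significant rise within the intervention arm could be reported as support for that expectation.

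There is a lesser point about precision. A between-group effect taken on raw values, either pooled over visits or at one visit, carries the full age spread of the sample in its error term.

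**Working it through.** **Plan's own figure.** For d = 0.5, 80% power and two-sided 0.05, the normal formula gives n = 2(1.960 + 0.842)²/0.5² = 62.8, so 63 per arm; the t-test gives 64. With 20% attrition, 64/0.8 = 80 per arm, as stated. I use 64 completers per arm below.

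**Assumptions.** The documents give no growth rate, SD or retest correlation. I assume:
- age uniform from 9 to just under 17, so its SD is 8/√12 = 2.31 years;
- correlation of the outcome with age r = 0.5 to 0.8;
- 12-month retest correlation ρ = 0.8 to 0.9;
- one year of growth within a child equal to the cross-sectional age slope.

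**Growth in one year.** Drift in SD units is r/2.31, which is 0.22 for r = 0.5 and 0.35 for r = 0.8. Against d = 0.5 that is 43% to 69%.

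**Single-arm time effect with no intervention effect.** The standardised change is drift/√(2(1−ρ)).
- r = 0.5, ρ = 0.8: 0.2165/0.632 = 0.342; with n = 64, power 0.77.
- r = 0.8, ρ = 0.9: 0.3464/0.447 = 0.775; power 1.00.
- With ρ = 0.7 the range is 0.60 to 0.94.

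A second model takes age uniform from 9 to 16 (SD 7/√12 = 2.02), yearly growth b of 0.25 to 1.0 within-age SD and residual correlation 0.7. It gives 0.73 at b = 0.25 and about 1.00 from b = 0.5.

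**Between-group contrasts.** In the second model, with a true effect of 0.5 within-age SD and 64 per arm:

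| b | Raw 12-month comparison, power (formula) | Group-by-time at 12 months, power (GEE simulation, 400 runs) |
|---|---|---|
| 0.25 | 0.71 | 0.940 |
| 0.5 | 0.51 | 0.945 |
| 0.75 | 0.34 | not simulated |
| 1.0 | 0.24 | 0.932 |

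With age variance removed, the single-visit comparison has power 0.81. The simulated interaction estimate averaged 0.497 to 0.503 when the truth was 0.5, and about 0 when it was 0. Its type I error was 0.045 to 0.07. Adding baseline age as a main effect left its rejection rates unchanged. By formula, its power falls to 0.72 in the least favourable case tried (residual correlation 0.5, b = 1.0, growth rates varying between children with SD 0.5b).

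**Gain from adjusting for baseline value and age.** With the total SD set to 1:
- a raw single visit has SD 1;
- a change score has SD √(2(1−ρ));
- the adjusted contrast has SD √[(1−r²)(1−p²)], where p = (ρ−r²)/(1−r²).

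| r | ρ | Change SD | p | Adjusted SD | SE cut v change | SE cut v raw visit |
|---|---|---|---|---|---|---|
| 0.5 | 0.8 | 0.632 | 0.733 | 0.589 | 7% | 41% |
| 0.5 | 0.9 | 0.447 | 0.867 | 0.432 | 3% | 57% |
| 0.8 | 0.8 | 0.632 | 0.444 | 0.537 | 15% | 46% |
| 0.8 | 0.9 | 0.447 | 0.722 | 0.415 | 7% | 58.5% |

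Much of the gain over a raw visit comes from the baseline value itself: adjusting for it alone gives SD √(1−ρ²), or 0.600 and 0.436 for ρ = 0.8 and 0.9. Sex is not in this calculation.

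**The case against.** A reader might infer that age differences swamp the intervention effect on these outcomes. The documents do not support that. Data analysis plans a group-by-time term. Stable age differences cancel in it, and growth is shared with a concurrent control arm on the same visit schedule. Only unequal growth rates between children add noise. This objection stands in full.

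Age adjustment is also a limited remedy. Baseline age and sex do not change within a child, so as main effects they cannot take growth out of the time effect, and baseline age did not sharpen the interaction. An age-adjusted single visit without the baseline value has SD √(1−r²) = 0.87 to 0.60. That is worse than the change score (0.63 to 0.45) at three of the four corners of the assumed range. This stands too, and it is why the fix must include the baseline value.

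Three further objections stand in part:
- Nothing in the plan says that benefit will be declared from time effects, and Implications sets no success criterion. But the plan does not rule it out either.
- Analysis on raw values is inferred from silence. These are, however, the only scoring and analysis rules given.
- The 77% to 100% models a single-arm test, whereas the plan's time effect is one term in a two-arm model. If that term averages both arms, growth is shared and n is larger, so the problem does not shrink.

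Finally, the clinic-to-home change affects both arms alike and cannot be sized from the documents. It confounds the time effect and does not bias the randomised contrast.

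**Conclusion.** The concern holds for the within-group time effects on three secondary outcomes. Under the assumed correlations they will usually be significant from growth alone, so they cannot support a claim of improvement. It also holds, as a matter of precision, for a raw pooled or single-visit between-group effect. Simple randomisation adds to that: with 80 per arm and age SD 2.02 to 2.31 years, the 95% range for a chance difference in mean age is ±1.96 × SD × √(2/80), about ±0.6 to ±0.7 years.

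It does not extend to the group-by-time contrast, which is unbiased and adequately powered in most scenarios tried. The percentages depend on assumed age and retest correlations; the direction of the problem needs only that children grow. The primary outcome, physical activity at 12 months, and the sample size are untouched. The change is worth making because the misreading is foreseeable and the cost is small.

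**What to change.** In Data analysis:

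1. State that within-group (time) effects are descriptive only. State that any claim of improvement rests on the randomised between-group contrast: group-by-time, or the baseline-adjusted difference between groups at 12 months.
2. For left HGS, right HGS and PEFR, estimate that contrast with the baseline value of the outcome, age at baseline and sex as covariates. The baseline value should enter as a covariate with the post-baseline visits as responses. Adding age and sex to a model that keeps baseline as a response would not sharpen the interaction.

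The cost is wording, a few extra model terms and the loss of within-arm significance statements. Baseline values are already scheduled, age is checked at eligibility and sex is routine baseline data, so nothing new is measured.

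### The primary outcome is physical activity at 12 months, but the Data analysis section does not say which GEE effect or contrast tests it.

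*Combined protocol and SAP*

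**What the plan says.** The Outcome measures section fixes one outcome at one visit: "The primary outcome measure is the level of physical activity of the survivors at 12 months after starting the intervention". Assessments take place at baseline and at 1, 3, 6 and 12 months.

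The Data analysis section gives a single specification for all outcomes: "Generalized estimating equation models will be used to examine the effect of the intervention on each outcome between groups over time". It adds that "between-group effects, within-group (time) effects, and interaction effects (group-by-time) will be examined", and sets every test at two-sided .05. It does not state whether time is categorical or continuous, which visit is the reference, whether baseline is an outcome row or a covariate, or which effect decides the primary outcome. No other section names a 12-month contrast.

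The Sample size calculation section describes its aim as follows: "To detect a statistically meaningful between-group difference with a moderate effect size". The effect is Cohen's d = 0.5, with 80% power and 20% attrition, giving 80 dyads per arm. It mentions no visit, number of repeated measurements or within-child correlation.

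**The concern.** The three listed effects, taken as overall tests, answer different questions from the primary outcome.

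- **Group effect.** This averages the difference over visits. If baseline is an outcome row, the average includes a visit before randomization, where only chance differences can exist.
- **Group-by-time effect.** This asks whether the difference changes between any visits, not whether there is one at 12 months.
- **Time effect.** This does not compare the arms.

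The protocol's own design makes disagreement between these tests plausible. Under Follow-up booster intervention, frequent contact lasts 6 months and is then cut to a minimum. The CUHK-PARCY asks about the past six months. The month-6 score therefore reflects the intensive phase and the month-12 score the low-contact phase, while the 1- and 3-month scores reach back before baseline. An effect that is present at month 6 and has faded by month 12 is a realistic outcome, and persistence to month 12 is what the stated primary outcome asks about.

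At stake is whether the trial's conclusion depends on a choice among tests that can disagree, made after the data are seen.

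**Working it through.** **1. The plan's own sample size.** Inputs from Sample size calculation: d = 0.5, two-sided alpha .05, 80% power, 20% attrition. A two-sample t-test at one time point needs 63.77, so 64 per arm. Then 64 / (1 − 0.20) = 80 per arm, 160 in total, which matches the plan exactly. With 64 completers per arm the power is 80.1% by t-test, or 80.7% by normal approximation. The calculation contains no repeated-measures term.

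**2. Assumptions for the comparison.** The documents give no correlations, visit-specific SDs or effect patterns. The following are assumed: 64 completers per arm, complete data, SD 1 at every visit, exchangeable correlation ρ of 0.3 / 0.5 / 0.7, categorical time, and baseline kept as an outcome row (five visits). The variance of a between-arm difference at one visit is then 2/64 = 0.03125.

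**3. Effect at month 6, none at month 12.** Assumed differences at baseline, 1, 3, 6 and 12 months are 0, 0.083, 0.25, 0.5 and 0 SD, with mean 0.167.

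- Sum of squared deviations from the mean: 0.1806.
- Noncentrality of the overall interaction (4 df): 32 × 0.1806 / (1 − ρ) = 8.25 / 11.56 / 19.26.
- Probability of a significant interaction: 62% / 79% / 96%.
- Probability that the 12-month comparison is significant: 5%, because there is no 12-month effect.

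**4. Same build-up, effect kept at month 12.** Assumed differences are 0, 0.083, 0.25, 0.5 and 0.5 SD, with mean 0.267.

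- Variance of the five-visit group effect: 0.03125 × (1 + 4ρ)/5, giving a standard error of 0.117 / 0.137 / 0.154.
- z = 0.267 / SE = 2.27 / 1.95 / 1.73, so power is 62% / 50% / 41%.
- If baseline is not an outcome row, the four-visit mean is 0.333. At ρ = 0.5 the standard error is √(0.03125 × 2.5/4) = 0.140, z = 2.39 and power is about 66%.
- The 12-month comparison has about 80% power at any ρ.

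**5. Error rate if either between-arm test could count.** If the tests are independent, 1 − 0.95² = 9.75%. The upper bound for two valid 5% tests is 0.05 + 0.05 = 10%.

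**6. Power of a named 12-month test.** Adjusting for baseline multiplies the variance by (1 − ρ²), where ρ is here the baseline-to-12-month correlation. Then z = 0.5 / √(0.03125 × (1 − ρ²)) = 2.96 / 3.27 / 3.96, and power is about 84% / 90% / 98%.

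**The case against.** **The model contains the comparison.** A reader might infer that the planned analysis cannot deliver the 12-month comparison. The documents do not support that. The section lists interaction effects in the plural. With categorical time and baseline as reference, one of them is the between-arm difference in change to 12 months. With 12 months as reference, the group coefficient is the 12-month difference itself. This stands: what is missing is the naming of the contrast.

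**The sizing is not tied to 12 months.** It is tempting to say that the trial was sized for the 12-month comparison. That is an inference. The sample size section names no visit, and its d is an average over physical activity, fatigue, strength and quality of life. The arithmetic shows only a two-group comparison at a single time point.

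**The plan already limits selective claims.** It fixes one outcome, one visit and one significance level, so claiming success from a month-6 difference with nothing at month 12 would contradict the Outcome measures section. This is a fair constraint, but it does not say which number in the GEE output is the primary result.

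**The figures rest on assumed inputs.** This also stands. Equal SD at baseline is doubtful in particular: entry requires no exercise in the previous 6 months and the scale covers that same period, so baseline scores may sit near the floor. A small baseline SD would bring the baseline-referenced 12-month coefficient close to the plain 12-month comparison.

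**Time trend.** A reader might expect a positive time effect in both arms because all children enter inactive. The documents do not say that controls will improve. The point needs only that a time effect does not compare arms.

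**Conclusion.** The point holds as an unspecified primary test. The endpoint is physical activity at 12 months, and the analysis lists overall group, time and interaction effects without saying which effect or contrast answers it. This is more than a missing detail, because the listed tests, run as overall tests, can give a different answer from the 12-month comparison in either direction. They can be significant when nothing remains at month 12, and they can miss a real 12-month effect.

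The percentages illustrate how far the answers can diverge. They are not predictions for this trial, and they depend on the assumed effect patterns, correlations, equal SDs, complete data and model coding. The error rate of up to about 10% applies only if either between-arm test could be called the primary result, which the plan neither states nor rules out.

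**What to change.** In Data analysis, name one primary test: the between-group difference in CUHK-PARCY at 12 months, estimated from the GEE with time as categorical and baseline CUHK-PARCY as a covariate, reported with a 95% CI and tested at two-sided .05. Label the overall group, time and group-by-time tests and the contrasts at other visits as supportive. State that the primary conclusion rests on the 12-month contrast alone.

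The cost is a few sentences. The same model yields the contrast and baseline is already collected, so no further data or participants are needed. The sample size stays at 160 dyads, with 80.1% power unadjusted and the higher adjusted figures shown above. If baseline scores cluster at the floor and the correlation is weak, the gain from adjustment shrinks towards zero, but the unadjusted power remains.
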